#### Analyses of outcome measures

Descriptive statistics will be used to summarize baseline characteristics. In the primary analysis, the risk difference with (two-sided) 95% confidence interval will be computed to compare the differences in 90-day recurrence risk between the two treatment arms, in both the intention-to-treat population and the per-protocol population. Regarding the primary analysis, multiple imputation will be used to deal with missing outcome data (i.e. missing information regarding CAUTI recurrence). For the primary outcome, three sensitivity analyses will be performed to account for missing data. In the first sensitivity analysis, a complete case analysis will be performed. Additionally, a worst-case and best-case scenario analysis will be performed, in which patients who drop out of the study before 90 days will be included under the assumption that they experienced a recurrence (worst-case scenario) or no recurrence (best-case scenario), respectively.

The primary analysis will not take patient characteristics into account, as these are expected to be balanced between treatment groups (by randomization). In a secondary analysis, multivariable analysis will be performed including variables that are associated with recurrence of CAUTI.

The secondary outcome time-to-resolution will be analysed using Kaplan Meier survival analysis. For patient-related outcomes measures, such as PROMIS and EQ-5D-5 L, repeated measures analyses will be performed to compare these outcomes between the groups. For these outcome measures, multiple imputation will be used to deal with missing outcome data. Process and resource related outcome measures will be analysed in the per-protocol population. In addition, a cost-effectiveness analysis from a societal perspective with a 6-month time horizon and a budget impact analysis will be performed.

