### Statistical analysis

#### Sample size

It is planned to recruit 300 participants (150 in each treatment arm). For both groups, we assume a recurrence rate of 10% [18] within 90 days after start of antibiotic therapy. Analyzing the data as a non-inferiority study, taking a non-inferiority margin of 10%, and a (one-sided) type-I error rate (alpha) of 2.5%, a study with 300 participants would have a power of approximately 80%. A power of 80% would indicate that the likelihood is 80% that the upper-limit of the 95% confidence interval for the 90-day risk difference will exclude a difference of 10% in favour of the control (replacement) group. To account for post-randomization exclusions, we plan to randomize 400 participants.

An interim analysis of the overall recurrence rate will be performed after 50% of the initially planned sample size has completed 90 days of follow-up. The interim analysis will not assess treatment effectiveness, and no early stopping for efficacy or futility is planned. The sole purpose of this interim analysis is to evaluate whether the observed overall recurrence rate aligns with the assumptions used for the sample size calculation. If the recurrence rate is found to be below 7.5%, the project group will consider whether an increase in the sample size is warranted.

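### The worst-case and best-case analyses give drop-outs the same outcome in both arms, so when drop-out is similar they cannot show retention drop-outs recurring more than replacement drop-outs

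*Protocol article*

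**What the plan says.** Under Analyses of outcome measures, the protocol article makes multiple imputation the primary handling of missing recurrence data. It names no missing-data mechanism and no departure from missing at random. It then says that "three sensitivity analyses will be performed to account for missing data": a complete-case analysis, a worst case and a best case. In the worst case, "patients who drop out of the study before 90 days will be included under the assumption that they experienced a recurrence (worst-case scenario"; in the best case the same patients count as having had none. Neither definition mentions treatment arm.

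The decision rule is under Sample size. Non-inferiority requires the following: "the upper-limit of the 95% confidence interval for the 90-day risk difference will exclude a difference of 10% in favour of the control (replacement) group". No drop-out rate is given anywhere. The increase from 300 to 400 randomised patients is attributed to post-randomisation exclusions.

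**The concern.** Non-inferiority is threatened by a positive risk difference, retention minus replacement. The missing-data pattern that could hide one is retention drop-outs recurring more often than replacement drop-outs. A rule that gives every drop-out the same value, whatever the arm, does not represent that pattern. Complete case does not either, and multiple imputation does not if it assumes missing at random.

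The trial is unblinded, and Strengths and limitations accepts that this may bias the reporting of recurrences. The section does not say that drop-out will depend on arm, but the setting makes the question fair. If retention is declared non-inferior and all three checks agree, a reader will take the result as robust to missing outcomes. The article's Implications section expects such a result to inform guidelines.

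**Working it through.** **Inputs from Sample size.** On size, "It is planned to recruit 300 participants (150 in each treatment arm"); on the event risk, "For both groups, we assume a recurrence rate of 10% [18] within 90 days after start of antibiotic therapy"; margin 10 points; one-sided alpha 2.5%, read from the upper limit of the two-sided 95% interval. **Assumed here:** the drop-out proportion *d* and the recurrence risks among drop-outs, since the article gives neither.

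**1. The plan's own figure.** Power at 150 per arm, 10% v 10%: Φ(0.10/√(2×0.10×0.90/150) − 1.96) = Φ(2.887 − 1.96) = 82.3%. Exact enumeration gives 81.9% with the Wald interval and 80.3% with the Newcombe interval. The stated power of about 80% is reproduced.

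**2. What the rules do to the contrast.** Let c be the recurrence risk in completers and q the risk in drop-outs, with drop-out d equal in both arms (R = retention, C = replacement).
- Worst case: [(1−d)c_R + d] − [(1−d)c_C + d] = (1−d)(c_R − c_C)
- Best case: (1−d)c_R − (1−d)c_C = (1−d)(c_R − c_C)
- Truth: (1−d)(c_R − c_C) + d(q_R − q_C)

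The term d(q_R − q_C) is absent from both scenarios. With unequal drop-out, the stated worst case falls short of the arm-opposed one (retention missing = recurrence, replacement missing = none) by exactly d_C. The two coincide only when d_C = 0.

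**3. Fixed example.** 150 per arm, 15 missing per arm, 10% observed recurrence (13.5/135) in both arms; Wald upper limits in percentage points.

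| Analysis | Retention v replacement | Upper limit |
|---|---|---|
| Complete case | 10% v 10% | 1.96×√(2×0.10×0.90/135) = 7.2 |
| Stated worst case | 19% v 19% | 1.96×√(2×0.19×0.81/150) = 8.9 |
| Stated best case | 9% v 9% | 1.96×√(2×0.09×0.91/150) = 6.5 |
| Arm-opposed | 19% v 9% | 10 + 1.96×√((0.1539+0.0819)/150) = 17.8 |

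The first three pass and the last fails. The stated worst case raises the limit from 7.2 to 8.9, so it is stricter than complete case, but only through the variance.

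**4. Unequal drop-out.** With 20 retention and 10 replacement drop-outs, and 10 and 15 observed recurrences, the stated worst case is 30/150 v 25/150: difference 3.3, upper limit 12.1. It fails.

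**5. How often the checks pass when the true difference is 10 points.** True risks 20% v 10%, 150 per arm, Wald limits, at least 200,000 simulated trials per row. With complete data the pass rate is about 2.7%.

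| Missing per arm | Recurrence in drop-outs, R v C | All three pass |
|---|---|---|
| 3% | 100% v 0% | 8% |
| 4% | 100% v 0% | 11% |
| 5% | 100% v 0% | 16% |
| 10% | 100% v 0% | 54% |
| 10% | 80% v 10% | 26% |
| 10% | 60% v 10% | 12% |
| 10% | 20% v 10% (non-informative) | 1.4% |

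In the 4% row the separate pass rates are 16% (complete case), 15% (worst case) and 18% (best case).

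**6. Varying the replacement arm.** Keep the loss of one in five retention recurrences (4% of that arm). The stated worst case then passes about 3% of the time in each of these settings: replacement loses nobody; 4% random loss is added in both arms; recurrers are lost at the same 20% rate in both arms. If replacement instead loses a random 4%, so that totals match, all three pass about 9% to 10% of the time.

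**The case against.** The strongest reply is that the stated worst case is a real check. It widens the interval: under true equality at 10% with 10% random drop-out it passes 60% of the time, against 82% with complete data. If informative loss raises drop-out in the retention arm, the rule penalises that arm and holds near the complete-data pass rate (step 6). This stands. A reader might infer that the planned checks do not challenge non-inferiority at all; the calculations do not support that.

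A second reply is that the simulated rates are not error rates of the trial. This also stands. The primary analysis is multiple imputation, which was not simulated, and the article does not make the claim depend on passing the sensitivity analyses. Reading 11% as an inflated type I error against 2.5% would be wrong. In that same example at least one of the three checks fails 89% of the time.

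Third, the size rests on assumptions. No drop-out rate is stated, and with equal drop-out, hiding the whole 10 points needs at least 10% missing with outcomes of 100% v 0%, or a 50-point gap at 20% missing. The protocol also asks physicians and general practitioners to report recurrences and centralises follow-up, which may limit missed events. This bears on likelihood; it does not change what the rules can detect.

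Finally, the imputation model and any delta adjustment are commonly left to an analysis plan that is not shown. Their absence from the article is not the point. The article itself defines both scenarios, without arm, and labels one of them the worst case.

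**Conclusion.** The point holds in a limited form. As written, the two scenarios multiply the completers' difference by (1−d) when drop-out is equal, and they cannot register a difference between arms in the drop-outs' outcomes. The label is accurate for non-inferiority only if the replacement arm has no drop-outs. The weakness appears when drop-out totals are similar but drop-outs' outcomes differ by arm. It is small or absent when drop-out is non-informative or clearly higher under retention.

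Under the assumed extreme (100% v 0%), all three checks pass a true 10-point excess 8% to 54% of the time over 3% to 10% missing per arm, against about 2.7% with complete data. Milder contrasts give less. That multiple imputation shares the gap assumes that it is done under missing at random, which the article does not say. A reader might infer that the primary test is invalid; nothing here shows that. The change is worth making before the data are seen, but the design does not depend on it.

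**What to change.** Keep the complete-case, worst-case and best-case analyses, and say in the text that the two scenarios apply one value to both arms.

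Add a delta-adjusted (tipping-point) analysis. Impute the replacement arm under missing at random, raise the imputed recurrence risk among missing retention patients in steps until the upper 95% limit reaches 10 points, and report the value at which that happens. Readers can then judge whether it is plausible. Report the number missing by arm beside it.

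Give the arm-opposed extreme only as an outer bound. It is severe: under true equality at 10% with random drop-out it passes about 37% of the time at 4% missing and 3% at 10%. It must not be read as a pass/fail test.

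The cost is a paragraph in the analysis plan and a few hours of programming on data already being collected. No patients or visits are added. The downside is that the result may look less secure than under the current checks.

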### Randomization

Patients will be allocated to the control or intervention group using the Castor Electronic Data Capture (EDC) system, in a 1:1 ratio. Stratified randomization will not be applied, as no single dominant prognostic factor for recurrence is known.

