#### Clinical data

At baseline, the following patient characteristics will be recorded: gender, age, height, weight, vital signs, social circumstances, medical history, medication use, catheter specific data (type of catheter, duration). The length of hospital stay, intensive care unit (ICU) admission during hospitalization, and type and treatment duration of antimicrobial agent(s) will additionally be collected.

Upon inclusion, CAUTI symptoms will be recorded, including onset or worsening of fever (> 38 degrees), rigors, altered mental status, malaise or lethargy with no other identified cause, flank pain, costovertebral angle tenderness, acute haematuria, pelvic discomfort, or suprapubic pain/tenderness. In patients with spinal cord injury increased spasticity, autonomic dysreflexia, or sense of unease will be assessed. Participants will be provided with a paper diary to record their symptoms for the first 14 days after start of antibiotic treatment. During each follow-up visit, CAUTI symptoms will be reassessed to track symptom duration and identify possible CAUTI recurrences.

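### The primary risk difference is left unadjusted because balance is expected; that justifies validity under intention-to-treat, but not the precision forgone, and it does not cover the per-protocol population

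*Protocol article*

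**What the plan says.** All references are to the Protocol article.

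- **Analyses of outcome measures** fixes the primary analysis as a risk difference with a two-sided 95% interval, computed in both the intention-to-treat and the per-protocol population. On covariates it states: "The primary analysis will not take patient characteristics into account, as these are expected to be balanced between treatment groups (by randomization".
- The same section adds a secondary analysis: "multivariable analysis will be performed including variables that are associated with recurrence of CAUTI". It names no variables, model or effect scale for it.
- **Randomization** gives the reason for simple allocation: "Stratified randomization will not be applied, as no single dominant prognostic factor for recurrence is known".
- **Clinical data** lists what is recorded at baseline, including gender, age and "catheter specific data (type of catheter, duration".
- **Sample size** powers the unadjusted comparison: "It is planned to recruit 300 participants (150 in each treatment arm"), with 10% recurrence assumed in both arms, a 10-point margin and a one-sided 2.5% error rate.

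**The concern.** The decision not to adjust is stated outright and comes with a reason, so it is more than a detail left for later. The reason answers a different question from the one that matters.

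- **Precision.** Expected balance means the unadjusted estimate is unbiased under intention-to-treat. Adjustment has a second purpose: it removes outcome variance explained by baseline variables, and it does so whether or not the arms are balanced.
- **Per-protocol population.** Membership depends on what happens after randomization, so balance by randomization cannot be invoked there. Yet the same sentence governs both populations.
- **No stratification.** The absence of one dominant factor explains why allocation was not stratified. Several moderate factors can still jointly explain some of the outcome, and adjustment uses exactly that.
- **Secondary model.** Covariates defined only by their relation to recurrence leave room for choice after the results are known, in an open-label trial.

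At stake are a somewhat wider interval than necessary in a trial powered at about 80%, a per-protocol result without baseline adjustment, and a secondary adjusted result whose content is not yet tied down.

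**Working it through.** **Inputs from the Sample size section:** 150 per arm; recurrence 10% in each arm; margin 10 points; one-sided alpha 2.5% (z = 1.96).

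**Input that the document does not give:** the share of outcome variance explained by baseline variables (R-squared). It is assumed here, over 0.02 to 0.10. At 10% incidence, a covariate score with a standard deviation of 0.5, 0.8 or 1.0 on the logit scale corresponds to an R-squared of about 0.02, 0.06 or 0.09.

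**Step 1: reproduce the plan's power.**

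SE = sqrt(2 × 0.10 × 0.90 / 150) = sqrt(0.0012) = 0.0346.

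Power = Phi(0.10 / 0.0346 − 1.96) = Phi(0.927) = 82.3%.

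Other usual variants at 150 per arm are exact binomial with a Wald interval 81.9%, exact binomial with a Newcombe interval 80.3%, and Farrington-Manning 78.8%. The stated figure of approximately 80% reproduces.

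**Step 2: effect of adjustment.** The variance is multiplied by (1 − R-squared):

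Power = Phi(0.10 / sqrt(0.0012 × (1 − R²)) − 1.96); half-width = 1.96 × SE; equivalent total n = 300 / (1 − R²).

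| Assumed R² | Power | 95% CI half-width (points) | Equivalent total n |
|---|---|---|---|
| 0 | 0.8230 | 6.8 | 300 |
| 0.02 | 0.8305 | 6.7 | 306 |
| 0.05 | 0.8418 | 6.6 | 316 |
| 0.10 | 0.8606 | 6.4 | 333 |

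The gain over R² = 0 is 0.8, 1.9 and 3.8 points, that is about 1 to 4 points, or the information of about 6 to 33 further patients.

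**Step 3: can the data support the model?** About 300 × 0.10 = 30 events are expected. In a simulation of the standardised risk difference with five covariates at 150 per arm, one-sided error at the margin was about 2.7 to 3.1%, against 2.6 to 2.8% unadjusted. Power changed by about 0, 1, 2 and 4 points as the assumed covariate strength rose from none to a logit standard deviation of 1.0.

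**Step 4: does open covariate choice matter?** A separate simulation assumed ten candidate variables, three of them prognostic, with R-squared about 0.05. It used a linear risk-difference model with robust standard errors. The Monte Carlo standard error of the error rates is about 0.2 points.

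| Approach | Power (10% v 10%) | One-sided error (10% v 20%) |
|---|---|---|
| Unadjusted | 82.5% | 2.6% |
| Variables named in advance | 84.4% | 2.7% |
| Variables selected at p < 0.10 for association with recurrence | 84.9% | 2.7% |
| Most favourable of several covariate sets | 87.3% | 3.7% |

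Mechanical selection on the outcome does almost no harm. The error rises when the covariate set is chosen after seeing what it does to the treatment comparison (the higher power in the last row comes with that inflated error). A list named in advance closes that route.

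**The case against.** The case for leaving the plan alone is substantial, and much of it stands.

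- **The unadjusted analysis is valid.** It is the quantity that was powered, there are no stratification factors to carry into the model, and chance imbalance is already reflected in the interval and the error rate. This stands for intention-to-treat.
- **The gain is small and assumed.** This also stands. At R-squared 0.02 it is under 1 point, and with non-prognostic variables there is none.
- **The covariate list may sit in an analysis plan that is not shown.** This stands for the secondary analysis: the absence of a list in a condensed article is not itself a fault.
- **About 30 events are too few for arm plus four or five covariates.** This does not stand. The simulated error rate stayed close to the unadjusted one, and power was not materially reduced even with useless covariates.
- **The trial began recruiting in April 2025.** Recruitment is planned to February 2028, so a change made before any data are examined by arm remains feasible.

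Two stronger readings are tempting. A reader might infer that covariates will be picked by their observed association in the trial data. The text states no screening rule, and its wording fits factors known beforehand equally well. A reader might also infer that the adjusted result will be an odds ratio that cannot be compared with the margin. The article names neither a logistic model nor an odds ratio for this analysis. The documents support neither reading.

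**Conclusion.** The point holds as a modest improvement to a stated choice. The reason given for not adjusting supports the validity of the intention-to-treat estimate. It does not address precision, and it does not reach the per-protocol population. The benefit is about 1 to 4 power points if baseline variables explain 2% to 10% of the outcome variance, a range that is assumed and not taken from the document. The 95% half-width would move from 6.8 to between 6.7 and 6.4 points.

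In the per-protocol population, adjustment addresses imbalance in the recorded variables only; it cannot remove selection related to unrecorded ones. The wording for the secondary model is open to later choice but does not commit to data-driven selection, and that analysis does not decide non-inferiority. It would be wrong to conclude that the unadjusted intention-to-treat result is biased or that the primary conclusion is threatened.

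**What to change.** Before any data are seen by arm:

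1. Name a short list of baseline variables already recorded, for example age, gender, catheter type and catheter duration.
2. Make the primary estimate the standardised (marginal) risk difference from a model with arm and these variables, with a robust 95% interval, in both the intention-to-treat and the per-protocol population. Judge it against the 10-point margin.
3. Report the unadjusted risk difference alongside in both populations. It remains the link to the sample-size calculation.
4. Replace the description of the secondary model's covariates with the same named list.

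No new data are needed. The cost is a documented change to the primary analysis, minor programming and slightly more complex reporting. If the primary analysis is to stay unadjusted, the same named list and risk-difference scale for the secondary analysis would still close the route to later choice, without the precision gain in the primary result.

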## Background

Due to the widespread use of urinary catheters, catheter-associated urinary tract infection (CAUTI) is the most common healthcare-associated infection [1]. As urinary catheter use is expected to rise with an aging population, the number of CAUTIs will likely increase accordingly [2]. CAUTIs can result in serious, sometimes fatal complications, including urosepsis [3–6].

To fasten recovery and reduce the risk of recurrent CAUTI, current guidelines recommend to replace the catheter at the onset of CAUTI when the indwelling catheter has been in place for more than two weeks [1, 6, 7]. This recommendation, however, is based on limited evidence as only four conflicting studies have been identified that investigate catheter replacement during CAUTI [8]. Current guidelines rely on only one of these four studies which is a small randomized controlled trial (RCT) that favoured catheter replacement [9]. The study reported shorter recovery times and lower recurrence rates in the replacement group compared to the retention group. These findings were contradicted by a second RCT [10], which found higher recurrence rates in the replacement group. However, in that study, antimicrobial treatment was shorter in the replacement group. Two observational studies found no effect of catheter replacement on either recurrence or symptom duration [11, 12], highlighting the paucity of the current state of evidence on catheter management during CAUTI.

In light of the limited evidence, a survey has been conducted to assess clinical practice regarding catheter management in CAUTI (manuscript in preparation [13]). It revealed considerable variation in catheter management practices among urologists, microbiologists, and internists. Urologists indicated more often that they routinely retain the transurethral catheter, compared to internists and medical microbiologists. The primary reasons for catheter replacement were the fact that it is a guideline recommendation and the expectation that replacement would be beneficial from a pathophysiological rationale. From a theoretical perspective, catheter replacement aligns with the principle of source control, as removal of the catheter may eliminate biofilm-associated pathogens that can persist during antimicrobial therapy and contribute to recurrent CAUTI [14]. Main reasons for retaining the catheter were the lack of scientific evidence supporting clinical benefit and the risk of procedural complications of the procedure.

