#### Exclusion criteria

A potential participant who meets any of the following criteria will be excluded from participation in this study:

Antibiotic treatment initiated more than 3 days prior to inclusion.Immunodeficiency: High-dose corticosteroid use (any equivalent of ≥ 20 mg prednisolone per day for > 4 weeks), severe primary immunodeficiency, organ transplant, neutropenia (absolute neutrophil count < 0.50 × 10⁹/L).Discontinuation of the indication for the indwelling catheter.A planned (routine) catheter replacement during antibiotic therapy.Contraindications for catheter replacement.Kidney catheters (nephrostomy or double-J catheter).Needing continuous bladder irrigations because of gross haematuria.Bladder stones.Pregnancy.A life expectancy of less than 90 days, as estimated by the treating physician.

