### Outcome measures

The primary outcome is a recurrent CAUTI within 90 days after completion of antibiotic treatment, defined according to the same IDSA-based clinical and microbiological criteria used for inclusion. The pathogen does not have to be identical to the causative pathogen that was identified during the first episode.

All participants are instructed to contact the central study team should they experience CAUTI symptoms. Additionally, the physicians at the participating centres and general practitioners are instructed to report potential recurrences among participants.

Secondary outcomes:

Patient-related outcomes: 30-day mortality, health-related quality of life assessed using the PROMIS and EQ-5D-5L questionnaires.Process-related outcomes: time to resolution of CAUTI symptoms, time to resolution of fever, complications of catheter replacement and severity of the complications (5-level Likert scale).Resource-related outcomes: length of hospital stay, ICU-admission during hospital stay, healthcare and societal cost using a selection of items relevant for this population of the medical consumption (iMCQ) and productivity (iPCQ) questionnaire.

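### Time to resolution is analysed by Kaplan-Meier with no provision for death before resolution; if deaths are censored as usual, the resolved proportion is modestly overstated

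*Protocol article*

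**What the plan says.** Under Analyses of outcome measures, the article states: "The secondary outcome time-to-resolution will be analysed using Kaplan Meier survival analysis". The Outcome measures section lists two outcomes of this kind: "Process-related outcomes: time to resolution of CAUTI symptoms, time to resolution of fever". I read the analysis sentence as covering both.

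Resolution is observed in two ways. Patients keep a paper diary to "record their symptoms for the first 14 days after start of antibiotic treatment", and the Clinical data section adds: "During each follow-up visit, CAUTI symptoms will be reassessed to track symptom duration".

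Death is foreseen. The Background says that "CAUTIs can result in serious, sometimes fatal complications, including urosepsis", and the secondary outcomes begin with "Patient-related outcomes: 30-day mortality". The Exclusion criteria remove patients with "A life expectancy of less than 90 days, as estimated by the treating physician", which should keep early deaths few.

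The article has no rule for death before resolution. Multiple imputation is stated for the primary outcome and the patient-reported outcomes. The worst-case and best-case analyses are stated for the primary outcome only.

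**The concern.** The event here is a good one, and death before it rules it out. If a death is censored at its date, Kaplan-Meier treats that patient as someone who would have gone on to resolve at the rate of those still followed. One minus the curve then estimates resolution in a hypothetical setting without deaths, not the share of patients who recovered.

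This matters somewhat because faster recovery is one of the two reasons the Background gives for replacing the catheter. A reader of the trial will look at the resolution curves, and at any proportion or median taken from them, to see whether retention slows recovery. Patients who died unresolved should count there as not recovered. Under the usual censoring they do not, and the arm with more such deaths gains more.

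**Working it through.** **Inputs.** From the article: 150 patients per arm (Sample size) and a 14-day diary (Clinical data). The article gives no rate of death or resolution, so those below are assumptions. It also gives no design figure for this outcome that could be reproduced; its approximate 80% power belongs to the primary comparison and plays no part here.

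**Formulas.** Take constant hazards, λ for resolution and μ for death while unresolved, read at t = 14 days.

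- λ = ln 2 / median
- Kaplan-Meier with deaths censored: 1 − KM = 1 − exp(−λt)
- Proportion actually resolved: CIF = λ/(λ+μ) × [1 − exp(−(λ+μ)t)]
- Proportion dead unresolved: D = μ/(λ+μ) × [1 − exp(−(λ+μ)t)]
- Overstatement = (1 − KM) − CIF

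**Direction, by counting.** Suppose that 5 of 150 die unresolved before anyone resolves, and 90% of the other 145 resolve. Kaplan-Meier reads 90.0%. The true share is 0.9 × 145 / 150 = 87.0%, so the excess is 3.0 points. With 1 such death it is 0.6 points, and with 8 it is 4.8.

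**Size by 30-day mortality while unresolved, q.** Here μ = −ln(1 − q)/30. With a median of 5 days, λ = 0.1386 per day and 1 − KM = 1 − exp(−0.1386 × 14) = 85.6%.

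| q | μ per day | CIF at day 14 | Overstatement |
|---|---|---|---|
| 2% | 0.00067 | 85.4% | 0.3 points |
| 5% | 0.00171 | 84.9% | 0.7 points |
| 10% | 0.00351 | 84.2% | 1.4 points |

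Across medians of 3 to 14 days and q from 2% to 20%, the day-14 overstatement runs from 0.2 to 3.0 points. At day 29, a later visit, it runs from 0.3 to 5.9 points.

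**Size by deaths actually occurring unresolved by day 14, D.** Here μ is solved so that D takes the stated value.

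| Median | D = 1% | 2% | 3% | 5% |
|---|---|---|---|---|
| 3 days | 0.9 | 1.7 | 2.6 | 4.4 |
| 5 days | 0.7 | 1.4 | 2.0 | 3.4 |
| 7 days | 0.5 | 1.1 | 1.6 | 2.7 |

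The entries are points of overstatement. The two tables differ only in their input. With a 5-day median, D = 5% needs μ of about 0.0084 per day, equivalent to 1 − exp(−30 × 0.0084), or about 22% mortality over 30 days while unresolved. With a 3-day median it needs about 31%. The right-hand column is therefore an upper case.

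**Between arms.** Bias common to both arms cancels in the comparison, so the yardstick is the standard error (SE) of the difference, √[CIF₁(1−CIF₁)/150 + CIF₂(1−CIF₂)/150]. Take equal resolution hazards and unresolved deaths of 5% against 1% by day 14.

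- Median 5 days: both Kaplan-Meier curves read 85.6%. The true proportions are 82.2% and 85.0%, so 2.7 points are hidden (from unrounded values). The SE is 4.3 points, and the ratio is 0.64.
- Median 7 days: the ratio is 0.43.
- Median 3 days: the ratio is 1.2.

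With 3% against 1%, the ratio is 0.32 at a 5-day median and 0.21 at 7 days. With 30-day mortality while unresolved of 5% against 10% (median 5 days), the hidden difference is 0.7 points. The article assigns process outcomes to the per-protocol population. If that leaves fewer than 150 per arm, the SEs rise and these ratios fall.

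**The case against.** The strongest objection is that Kaplan-Meier does not itself cause the bias. The cause is a censoring rule that the article never states. Patients who die can be held in the risk set as unresolved to the end of the window, and the curve is then correct. A condensed article may leave such a rule to a fuller document that is not shown. This stands in part: nobody can say from the article that deaths will be censored at their date. But the article does name its estimator, and the default use of that estimator gives the wrong proportion for a favourable event that death precludes. A better choice is available at almost no cost, so the point is more than a request for detail.

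A reader might also infer that Kaplan-Meier would make retention look as good as replacement even if retention slowed recovery. The article does not support that. Unresolved patients remain in the risk set until they die, so a lower resolution rate still shows. The curves coincide only if the resolution hazards are equal, as in the worked example. A log-rank or cause-specific comparison remains valid as a comparison of rates.

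Nor would deaths be hidden from the trial, because 30-day mortality is its own secondary outcome. The exclusion of patients with short life expectancy, and the requirement that patients can give consent, both argue for few early deaths. These limits stand, and they keep the point small.

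**Conclusion.** The point holds as a minor improvement to two secondary outcomes. If deaths are censored at their date, one minus Kaplan-Meier overstates the proportion resolved whenever someone dies unresolved and others resolve later. The affected quantities are proportions and medians read from the curve.

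The plausible size at day 14 is roughly 0.3 to 1.4 points, rising to about 3.4 points in the upper case. Both figures assume a 5-day median and constant hazards. The distortion between arms exceeded one SE of the difference only with very fast resolution combined with a wide gap in unresolved deaths (3-day median, 5% against 1%). All of these rates are assumptions. The primary risk difference and its power are untouched.

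**What to change.** Either of two changes to the sentence on time to resolution, for both symptoms and fever, is enough:

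- Report the cumulative incidence of resolution (Aalen-Johansen) with death before resolution as a competing event, and compare the arms on the resolved proportion at day 14. Gray's test is a reasonable companion.
- Keep Kaplan-Meier, but state that patients who die unresolved stay in the risk set as not resolved to the end of the window.

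If a fuller analysis plan already contains such a rule, the article only needs to say so. The cost is one sentence, a standard routine and slightly lower resolved proportions. Dates of resolution and death are all it needs, so no further data collection is required.
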